##### Adherence analyses

The relationships between medication adherence determinants and behaviours and asthma-related outcomes will be investigated based on a theoretical model of asthma management. These analyses will further examine the hypothesis that LABA risk in asthma may be partly owing to suboptimal adherence to ICs, with initial symptoms masked by concomitant LABA use, leading to severe and sudden SAEx. Moreover, they also aim to identify important and changeable causes of nonadherence from a patient, caregiver and HCP perspective, with a view to improving adherence support in primary care.

### Ethics

ASTRO-LAB study has been approved by Ethics and Regulatory Boards in both countries.

## Discussion

ASTRO-LAB presents several innovative aspects that will allow a unique perspective on LABA safety and asthma management, in real-life conditions. Data will be collected from complementary sources to assess patients’ drug exposure. This will allow assessing more elaborated markers of drug exposure and adherence to check the robustness of our findings.

The direct assessment of patients’ adherence to therapy, including potential changes over time, will enable us to distinguish the confounding role of inadequate adherence to ICs from LABA-specific risk, as differential adherence between LABAs and ICs may contribute to the occurrence of SAEx for patients receiving both classes in separate canisters.

Methodological limitations and practical difficulties must be acknowledged. The scarcity of patients prescribed LABAs in monotherapy may prevent any reliable conclusion for this non-recommended therapy pattern.^6,15^ Pre-selection process between countries will differ: pre-existing prescribing database in the UK versus an *ad hoc* prescription register collected by physicians themselves purposely for the study. This difference is owing to practical access to existing prescribing data (possible in the UK only, in the context of ASTRO-LAB). Nevertheless, the same inclusion/exclusion criteria will be eventually applied to all patients in both countries. A potential bias inherent to prospective studies will be that patients’ interaction with field study procedures (for example, questionnaires and CATIs) may modify their behaviours and beliefs regarding medication intake. Nonetheless, this potential bias will influence all treatment groups equally.

Practical difficulties have to be addressed in this multifaceted project. Different national regulatory requirements and health care systems between France and the United Kingdom compelled us to consider specific recruitment processes for each country, while attempting to maintain the two processes as similar as possible to minimise bias.

Given its unique perspective on asthma care, ASTRO-LAB will provide new information on LABA safety of substantial interest to regulators, HCPs, patients and the scientific community. Moreover, developing new methods of assessing drug exposure and adherence will make a valuable contribution beyond the field of asthma care. The investigation of multifaceted insight into asthma management in two different medical systems may be informative for the improvement of asthma care.

Further information can be found in the Supplementary Information.

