#### Electronic medical records/claims data

The Health Improvement Network data will be available in the UK, whereas refill and hospitalisation data will be obtained from the National Health Insurance System (SNIIRAM) in France.

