#### Medication use and adherence

Medication use will be assessed via CATIs for each daily inhaled medication separately, with questions referring to different time intervals and behaviours: number of doses used the day before the interview, number of days with 0% and 100% adherence during the previous 7 days, number of days of non-use during the previous 4 weeks, treatment interruptions longer than a week in the previous 4 months, and medication overuse (for a specific time interval or occasional) in the previous 4 months. Patient/caregiver-reported drug exposure and adherence will be computed via algorithms developed in preliminary analyses.

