#### Planned analyses

##### Safety analyses

*Between-group comparisons*. As first approach, the time to the occurrence of the first SAEx will be compared between the initial exposure groups (ICs without LABAs group as reference) with survival analyses (Kaplan–Meier, Cox Model). The total number of SAEx per patient during a 12-month period will be also compared using Poisson regression.

*Cohort analyses with time-dependent variables*. Patients’ actual exposure to LABAs and ICs may change over follow-up owing to the prescriber or patient. In these analyses, such changes will be taken into account. Time-dependent variables, reflecting LABAs or ICs exposure over follow-up, will be constructed. The association between exposure to LABAs over time and the occurrence of SAEx will be investigated, after adjusting in particular for concomitant exposure to ICs. Survival analyses and hierarchical longitudinal models will be applied. Different markers of drug exposure and adherence will be successively explored.

*Case–crossover study and nested case–control study approaches*. As in a case–crossover design patients are their own controls, LABAs and ICs studied drug exposure patterns occurring just before a SAEx (case period) will be compared with those observed during a preceding regular CATI with no SAEx reported (control period), thus eliminating any potential influence of patients fixed characteristics. A nested case–control study approach will be also considered.

*Adjustment for asthma baseline severity*. Analyses will be adjusted for the different markers of asthma baseline severity, as it is a potential confounding factor when assessing LABA-related risk, except for the case–crossover approach.

Complementary analyses will be considered with the French patients, using claims data.

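### Interview-reported adherence cannot by itself separate inhaled-corticosteroid under-use from a LABA-specific risk; adjusting for it leaves a residual of unknown size and direction

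*Protocol article*

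**What the plan says.** All places are in the protocol article.

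- **Aims** names as a key question whether any LABA-associated risk is explained by poor adherence to ICs.
- **Discussion** states, without qualification, that direct assessment of adherence "will enable us to distinguish the confounding role of inadequate adherence to ICs from LABA-specific risk".
- **Medication use and adherence** describes that assessment: "Medication use will be assessed via CATIs for each daily inhaled medication separately". The items cover recall windows from the previous day to the previous four months, and "Patient/caregiver-reported drug exposure and adherence will be computed via algorithms developed in preliminary analyses". No accuracy is given.
- **Safety analyses** relates LABA exposure over time to severe exacerbations (SAEx) "after adjusting in particular for concomitant exposure to ICs", and adds that "Different markers of drug exposure and adherence will be successively explored".
- **Electronic medical records/claims data** provides UK primary care records, and "refill and hospitalisation data will be obtained from the National Health Insurance System (SNIIRAM) in France". Their role in the safety analyses is modest: "Complementary analyses will be considered with the French patients, using claims data". The Discussion presents the multiple sources as a robustness check: "This will allow assessing more elaborated markers of drug exposure and adherence to check the robustness of our findings".
- The limitations in the **Discussion** cover the effect of study contact on behaviour, which is said to act equally in all groups. They do not mention error in reported use.

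**The concern.** Adjusting for a variable recorded with error controls only part of the effect of the true variable. The Background accepts that irregular IC use causes exacerbations. If true IC under-use differs between LABA-exposed and LABA-unexposed patients or periods, the uncontrolled part appears in the LABA coefficient.

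Trying several markers in turn does not remove this, because each model still adjusts for an imperfect marker. Agreement between interview-based markers may reflect error that they share.

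The answer to the key question is at stake. A residual association could be reported as LABA-specific when it is leftover confounding by IC under-use, or a real association could be masked. The study addresses its results to regulators, so the label matters.

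**Working it through.** The plan gives no figure on this point, so there is none to reproduce. The check asks how much of the IC effect survives adjustment when the true LABA ratio is 1.00.

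**Inputs, all assumed** because the article gives none of them: true IC under-use is u1 in the LABA group (separate canisters) and u0 in the ICs-only group; under-use multiplies SAEx risk by R = 2.5; a true under-user reports under-use with probability Se; an adequate user reports adequate use with probability Sp = 0.95; groups are of equal size. Se and Sp are the same in both groups.

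**Crude ratio** = [1 + u1(R − 1)] / [1 + u0(R − 1)]. With u1 = 0.50 and u0 = 0.25 this is 1.75 / 1.375 = 1.273.

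**Adjusted ratio**: Mantel-Haenszel ratio over the two strata of reported use. For group g, with risk expressed relative to an adequate user:

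- reported under-use: share p = u·Se + (1 − u)(1 − Sp); events c = u·Se·R + (1 − u)(1 − Sp)
- reported adequate: share p = u(1 − Se) + (1 − u)Sp; events c = u(1 − Se)R + (1 − u)Sp
- adjusted ratio = Σ[c1·p0/(p1 + p0)] / Σ[c0·p1/(p1 + p0)]

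**Worked case, Se = 0.60:**

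- Reported under-use: p1 = 0.325, p0 = 0.1875, c1 = 0.775, c0 = 0.4125. Terms: 0.2835 and 0.2616.
- Reported adequate: p1 = 0.675, p0 = 0.8125, c1 = 0.975, c0 = 0.9625. Terms: 0.5326 and 0.4368.
- Adjusted ratio = (0.2835 + 0.5326) / (0.2616 + 0.4368) = 1.169.
- Share of the log excess remaining = ln 1.169 / ln 1.273 = 65%.

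**Results, true LABA ratio 1.00:**

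| Under-use, LABA vs reference | Crude | Se 0.40 | Se 0.60 | Se 0.80 | Se 0.90 |
|---|---|---|---|---|---|
| 50% vs 25% | 1.27 | 1.22 | 1.17 | 1.11 | 1.07 |
| 45% vs 30% | 1.16 | 1.12 | 1.10 | 1.06 | 1.04 |
| 30% vs 60% (reversed) | 0.76 | 0.80 | 0.84 | 0.89 | 0.92 |

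In the first row 82%, 65%, 42% and 29% of the log excess remains. In all three rows the adjusted ratio is exactly 1.00 if Se and Sp are both 1. The third row represents LABA-unexposed time in which ICs are also under-used; the residual is then a false deficit.

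**Second set of assumptions:** under-use 60% vs 40% and R = 2, crude ratio 1.143. At Se/Sp of 0.90/0.95, 0.80/0.90 and 0.60/0.90 the adjusted ratios are 1.039, 1.071 and 1.103, so 28%, 51% and 73% of the log excess remains. For scale, take 2,200/3 × 0.8 = 587 patients per group and the 24% reference risk from the Sample size section. A two-proportion test would then find a false excess with probability of about 6%, 10% and 16%, against a nominal 2.5% in that tail.

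**The case against.** The strongest reply is that the plan does not rest on interviews alone, and most of that reply stands.

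- **Other data sources.** UK records and French refills fail in different ways from recall, so agreement across them is informative. They show supply rather than use, however, and the French claims analyses are complementary and only to be considered.
- **Fixed-dose combination group.** One inhaler delivers both drugs, so taking LABA without IC is excluded in that group. Its overall IC adherence may still differ from that of ICs-only users.
- **Case-crossover analysis.** Comparing patients with themselves largely holds a stable reporting habit constant. Its exposure still comes from interviews, and the case-period report is collected after the SAEx, so time-varying recall error remains.
- **The model is simple.** It uses one yes/no report and two fixed groups with LABA exposure known, whereas the planned adjustment is time-dependent and both drugs are reported in the same interview. It therefore illustrates the mechanism and does not forecast this study's bias.

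A reader might infer that most of the IC effect is bound to remain, or that any LABA excess found will be false. The documents support neither. They give no reporting accuracy, no adherence by group and no effect of under-use; with very good reporting the remainder is under a third. Error that differs by group or follows a SAEx can push the estimate either way. Nor is the absence of an error-correction method a fault here, since an article may leave that to an analysis plan. The fault lies in the unqualified claim.

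**Conclusion.** The concern holds in a limited form. The Discussion credits the design with an ability to separate two explanations that interview-reported adherence cannot deliver, and reporting error is not among the stated limitations. Under the assumed inputs with no LABA effect, the adjusted ratio lies between 1.07 and 1.22 for the larger contrast and between 1.04 and 1.12 for the milder one, over reporting sensitivity of 90% down to 40%. With the contrast reversed it lies between 0.80 and 0.92. Every input is an assumption, so neither the size nor the sign of the actual residual is known. The other design elements narrow the problem without closing it.

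Separately, the Aims treat differential adherence as a possible mechanism while the Discussion calls it confounding. The meaning of the adjusted estimate would need stating even if reports were error-free.

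**What to change.** 1. **Discussion:** replace the claim with wording such as *will help to assess, but cannot fully separate*, and list error in reported medication use as a limitation.
2. **Safety analyses:** add a quantitative bias analysis of the IC-adjusted LABA estimate over a stated range of reporting sensitivity and specificity (for example 40–95%), including error that differs between groups.
3. **Safety analyses:** repeat the adjusted model with refill-based IC coverage in the French patients who have claims data. Treat this as a sensitivity analysis and not as calibration to a gold standard, because refills show supply rather than use.
4. **Interpretation:** describe a residual association as LABA-specific only if it persists across plausible reporting error and agrees with the fixed-dose combination and case-crossover results.

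No new data collection is needed. The cost is a little extra analysis and a less firm conclusion.

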## Figures and Tables

**Figure 1 fig1:**
[figure not shown]
Study flowchart for patient enrolment and follow-up.

**Figure 2 fig2:**
[figure not shown]
Summary of patient- and physician-reported data at inclusion and during follow-up.
